## Abstract

**Background:**

Many patients who survive the intensive care unit (ICU) experience long-term complications such as peripheral neuropathy and nephropathy which represent a major source of morbidity and affect quality of life adversely. Similar pathophysiological processes occur frequently in ambulant patients with diabetes mellitus who have never been critically ill. Some 25 % of all adult ICU patients have diabetes, and it is plausible that ICU survivors with co-existing diabetes are at heightened risk of sequelae from their critical illness.

ICU follow-up clinics are being progressively implemented based on the concept that interventions provided in these clinics will alleviate the burdens of survivorship. However, there is only limited information about their outcomes. The few existing studies have utilised the expertise of healthcare professionals primarily trained in intensive care and evaluated heterogenous cohorts. A shared care model with an intensivist- and diabetologist-led clinic for ICU survivors with type 2 diabetes represents a novel targeted approach that has not been evaluated previously. Prior to undertaking any definitive study, it is essential to establish the feasibility of this intervention.

**Methods:**

This will be a prospective, randomised, parallel, open-label feasibility study. Eligible patients will be approached before ICU discharge and randomised to the intervention (attending a shared care follow-up clinic 1 month after hospital discharge) or standard care. At each clinic visit, patients will be assessed independently by both an intensivist and a diabetologist who will provide screening and targeted interventions. Six months after discharge, all patients will be assessed by blinded assessors for glycated haemoglobin, peripheral neuropathy, cardiovascular autonomic neuropathy, nephropathy, quality of life, frailty, employment and healthcare utilisation. The primary outcome of this study will be the recruitment and retention at 6 months of all eligible patients.

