### Outcome measures

All patients in the intervention and control groups will be contacted by mail and telephone and invited back at 6 months after hospital discharge for assessment. Patients will be assessed by two blinded assessors (an intensivist and a diabetologist) who were not present at the follow-up clinic. Before undergoing this assessment, patients in the intervention group will be instructed not to refer to their prior attendance at the follow-up clinic so that the assessors remain blinded.

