Additional secondary outcomes related to functioning in the community and healthcare resource use will also be collected. These outcomes may also serve as secondary outcomes in a subsequent larger study. The degree of frailty will be assessed using the Canadian Study on Health and Aging Clinical Frailty Scale [55], a validated tool which has previously been used in the Australian ICU setting [71] and may predict outcomes in critically ill patients [72]. Employment status will be recorded. Healthcare utilisation data will be collected prospectively using patient monthly diaries and corroborated with hospital inpatient and outpatient clinical records and self-reports at scheduled study visits. This validated approach provides patient-specific and activity-based resource-use data after hospital discharge [6, 73]. We will specifically collect data about hospital and ICU readmissions; inpatient and outpatient rehabilitation service utilisation; hospital emergency room and outpatient clinic visits; general practitioner and specialist visits; diagnostic tests; home care services and provision of specialised medical equipment. If required when an inpatient admission occurs, we will obtain (with the patient’s consent) the medical record to confirm the dates of admission, reason for admission and types of treatment received.

The outcome measures will be taken 6 months after hospital discharge by blinded assessors. EuroQol EQ-5D-5L scores, employment status and healthcare utilisation data will also be collected during the follow-up clinic visit 1 month after hospital discharge in the intervention group. Patients failing to attend the assessment visit will be contacted by telephone and/or mail, provided with the relevant questionnaires for completion, and asked to make their diaries available to the research team. Reasons for non-attendance at the clinic and the assessment appointment will be recorded.

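### Healthcare utilisation is given to the blinded 6-month assessors, which conflicts with the instruction that patients keep silent about the study clinic

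*Protocol article*

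**What the plan says.** The Abstract (Methods) lists what patients are to be "assessed by blinded assessors for glycated haemoglobin, peripheral neuropathy, cardiovascular autonomic neuropathy, nephropathy, quality of life, frailty, employment and healthcare utilisation". The body, under Secondary outcomes, makes no exception: "The outcome measures will be taken 6 months after hospital discharge by blinded assessors".

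The same section defines utilisation to include "hospital emergency room and outpatient clinic visits; general practitioner and specialist visits; diagnostic tests". The data come from monthly patient diaries, "corroborated with hospital inpatient and outpatient clinical records and self-reports at scheduled study visits".

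Outcome measures describes how blinding is kept. There are two safeguards. The first is the choice of assessors: "Patients will be assessed by two blinded assessors (an intensivist and a diabetologist) who were not present at the follow-up clinic". The second is that intervention patients are "instructed not to refer to their prior attendance at the follow-up clinic so that the assessors remain blinded".

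At 1 month, "healthcare utilisation data will also be collected during the follow-up clinic visit 1 month after hospital discharge in the intervention group". Table 2 lists review of the utilisation diary among the clinic intensivist's tasks.

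**The concern.** The trial is open-label for patients, so blinding at 6 months depends on what the assessor is told or sees. The intervention (Intervention group, Table 2) is a hospital follow-up clinic with an intensivist and a diabetologist, preceded by a blood panel. It therefore falls within what utilisation is meant to capture: an outpatient visit, specialist reviews and diagnostic tests. Asking the blinded assessor to obtain that information works against the instruction on which blinding relies.

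Two things are at stake. Outcomes that need the assessor's judgement could be scored with allocation known. Alternatively, utilisation could be under-reported in the intervention arm only, because only those patients have something to leave out.

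**Working it through.** The article gives no figure to reproduce, and the point depends on no power, rate or effect size. The check sets the instructions side by side.

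1. **Who takes utilisation at 6 months.** The Abstract names it on the blinded assessors' list. Secondary outcomes gives the outcome measures to blinded assessors as a group. Nothing assigns utilisation to anyone else.
2. **What utilisation contains.** It covers "hospital emergency room and outpatient clinic visits; general practitioner and specialist visits", with no exclusion of the study clinic.
3. **How the assessor could learn of it.** Self-report at scheduled study visits is a named source, and the 6-month assessment is such a visit. Disclosure therefore does not require the assessor to open a diary or an outpatient record.
4. **What the patient is told.** Intervention patients must not refer to the clinic (Outcome measures).
5. **The result.** A patient asked at the blinded visit for all outpatient and specialist visits has two options. Full reporting can disclose allocation. Leaving the clinic out protects blinding but makes the self-report incomplete, in one arm only.
6. **Whether another rule resolves it.** Using assessors who did not staff the clinic does not help, because the information comes from the patient. The article does not exclude study-clinic visits, withhold diaries, or require examined outcomes to be finished before utilisation is asked about.
7. **Which outcomes are exposed.**

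| Outcome at 6 months | Scope for assessor influence |
|---|---|
| Glycated haemoglobin, creatinine, urine albumin | Little: laboratory values |
| EQ-5D-5L, SF-36 | Little: completed by the patient |
| Clinical Frailty Scale | Yes: judged |
| Michigan neuropathy instrument, examination part | Yes: examined |
| Recruitment and retention (primary) | Not assessor-rated |

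8. **How many patients.** The article does not say. The ceiling is the number of intervention patients who attended the clinic and are assessed at 6 months. As an illustration, take the minimum success figures in the Analysis plan and assume an even split. Of 40 recruits, 40 × 0.5 = 20 would be in the intervention arm; of 32 with complete data, 32 × 0.5 = 16. Simple randomisation can give a different split, and not everyone need attend or disclose, so these are upper limits under the stated assumptions and not estimates of unblinding.
9. **Ascertainment at 1 month.** The early collection and diary review happen in the intervention arm only. The monthly diaries and record checks are not restricted to one arm.

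**The case against.** The strongest reply is that the article never says the assessors themselves handle the diaries or check outpatient records. The collection sentence names no collector. For patients who miss the visit, diaries go to the research team, and a research coordinator is already employed for data management. Who handles these papers is the kind of detail that a condensed article leaves to the full protocol. This stands in part. A reader might infer that the assessors read diaries and records, and the document does not support that. It does, however, place utilisation on the blinded assessors' list and name self-report at study visits as a source, so the conflict is in the text itself and is not an omission.

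A reader might also infer that blinding is defeated altogether. That does not follow. Controls also see general practitioners and specialists under usual care, so an outpatient visit or blood test does not by itself reveal the arm. The article does not show whether a diary entry would name the clinic, and several outcomes leave the assessor little room for influence.

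Third, the consequences within this study are small. The primary outcomes do not depend on the assessor. The scientific outcomes listed in the Analysis plan, including the Michigan score, are reported pooled over both arms, and utilisation is reported descriptively. The SF-36, from which the article takes the intended primary outcome of the larger trial, is completed by the patient. All of this stands and limits the weight of the point.

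Finally, it might be said that study-clinic visits inflate utilisation in the intervention arm. The clinic is the health-service intervention, so counting its use is a legitimate choice. What is needed is that its share can be separated.

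**Conclusion.** The point holds as a conflict between instructions. Following the article as written either gives the assessor information that can disclose allocation, or leaves study-clinic use out of the self-report in one arm. That unblinding will happen is an inference, and its frequency cannot be derived from the document.

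The exposure is confined mainly to judged or examined outcomes, namely the Clinical Frailty Scale and the examination part of the Michigan instrument. Feasibility conclusions on recruitment and retention are unaffected.

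It still deserves correction for two reasons. The Analysis plan pools the scientific outcomes so that these participants' data can enter the main trial, where any assessor bias would fall into a between-arm comparison. The Discussion also counts blinded outcome assessment as a methodological strength, a claim that the present division of tasks does not secure. The conclusion assumes that the full protocol does not already assign utilisation elsewhere; if it does, the article's wording needs only to be aligned with it.

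**What to change.** - Remove healthcare utilisation from the blinded assessors' tasks, in the Abstract and under Secondary outcomes.
- Have the existing research coordinator collect diaries, record checks and self-report in both arms, outside the blinded assessment.
- Withhold diaries and clinic notes from the assessors until their forms are complete.
- Record study-clinic visits and study-ordered tests as a separate category, so that utilisation can be reported with and without them.
- Record each assessor's guess of allocation at 6 months. Whether blinding held is useful feasibility information for the main trial.
- State in the report that the 1-month diary review took place in the intervention arm only. Do not add a matching 1-month call to controls: it would alter usual care and could affect retention, a primary outcome. Rely on the monthly diaries and record checks, which are not restricted to one arm.

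The cost is a little more coordinator time and one extra form item. Clinical care does not change in either arm.

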**Discussion:**

This study will provide preliminary data about the potential effects of critical illness on chronic glucose metabolism, the prevalence of microvascular complications, and the impact on healthcare utilisation and quality of life in intensive care survivors with type 2 diabetes. If feasibility is established and point estimates are indicative of benefit, funding will be sought for a larger, multi-centre study.

**Trial registration:**

ANZCTR ACTRN12616000206426

## Background

Acute hospital mortality for patients admitted to intensive care units (ICUs) has decreased substantially in the past two decades [1]. However, longer-term outcomes for those who survive hospital discharge remain poor, with approximately 40 % of patients dying in the 5 years after hospital discharge [2, 3]. This ‘legacy effect’ of critical illness on the risk of death is consistent across studies from various regions and appears to persist for at least 15 years after the index admission [2–4].

In addition to being a strong predictor of death, an episode of critical illness leads to substantial morbidity, with survivors frequently experiencing long-term physical and neuropsychiatric problems including weakness, impaired physical function, depression, anxiety, and cognitive dysfunction [5]. Moreover, the morbidity of chronic illness is exacerbated by ICU admission. For example, in an important longitudinal study of 109 ICU survivors followed for 5 years, for each additional chronic illness, healthcare expenditure increased threefold after hospital discharge [6]. Because the long-term effect of a single episode of critical illness on health is substantial, and the costs associated with care of survivors, particularly those with pre-existing chronic illnesses, are considerable, there is an urgent need for interventions that modify these outcomes in patients with chronic illnesses.

Diabetes, particularly type 2 diabetes, is a frequently co-existing illness in critically ill patients, with a reported prevalence ranging from 12 to 30 % in observational studies [7–11]. However, it is likely that the true prevalence has been under-represented in these studies due to diabetes that is either not documented or recognised [12]. While diabetes per se has been identified as a risk factor for the development of critical illness, as well as the severity of the illness [13, 14], and the presence of diabetes is associated with a greater number of other co-existing chronic illnesses, it is surprising that there does not appear to be any association between the presence of diabetes and the risk of death within the index hospital admission. Indeed, several studies have now reported that patients with diabetes have comparable, or slightly lower, ICU and hospital mortality rates when compared to patients without diabetes [13–16]. While it is plausible that ICU survivors with diabetes are more likely to experience greater long-term morbidity and mortality than survivors without diabetes, this has not been evaluated and the long-term effects of critical illness on patients with diabetes are unknown.

It is notable that many of the complications which occur in the critically ill are also well-recognised microvascular complications which are prevalent in ambulant patients with diabetes. Autonomic neuropathy, sensorimotor peripheral neuropathy and nephropathy are all common in survivors of critical illness [17–19] as well as in patients with type 2 diabetes who have never been critically ill [20]. It would, therefore, not be surprising if these disease processes are additive, or even synergistic, so that an episode of critical illness has the potential to exacerbate any underlying complications of diabetes, but this has not previously been investigated.

Critical illness polyneuropathy affects up to half of ICU survivors [18]. Critical illness polyneuropathy is an axonal degenerative condition and, although multiple mechanisms are implicated, hyperglycaemia is strongly associated with its development [18, 21, 22], as is well established to be the case for the microvascular complications of diabetes [23, 24]. Patients with critical illness polyneuropathy experience weakness, which can be profound and associated with considerable disability. Recovery is typically slow and may occur over years; indeed in some cases, the polyneuropathy never resolves completely [25]. Similarly, acute cardiovascular autonomic neuropathy also occurs frequently during critical illness, even in those not known to have diabetes, and is strongly associated with day-28 mortality [17]. In ambulant patients with type 2 diabetes, cardiovascular autonomic neuropathy is now recognised as an important predictor of cardiovascular death and has a greater impact than ‘traditional’ cardiovascular risk factors such as hypertension and hyperlipidaemia [26–28]. During critical illness, patients also often have markedly delayed gastric emptying [29], and survivors frequently report sexual and bladder dysfunction [30, 31], all of which may be manifestations of underlying autonomic neuropathy similar to that which occurs in patients with diabetes [32]. However, whether autonomic neuropathy occurs frequently in ICU survivors with pre-existing type 2 diabetes, as well as the natural history and clinical implications of this condition, are unknown.

In critically ill patients who develop acute kidney injury requiring renal replacement therapy, short-term mortality is very high [19], even in those who survive hospitalisation [33]. Moreover, survivors also report reductions in physical function and mental health 3 years after ICU discharge [34, 35], long-term mortality rates are considerable (>60 %) and chronic albuminuria is present in almost half of those alive at 4 years [33]. The latter is known to be an independent risk factor for cardiovascular disease, requirement for dialysis, and death in cohorts of patients with chronic kidney disease, as well as in epidemiological studies of the general population [36, 37]. It is conceivable, therefore, that longitudinal outcomes will be worse in critically ill patients with diabetes, particularly given that albuminuria is a key feature of diabetic nephropathy.

Microvascular complications, including cardiovascular autonomic neuropathy, account for much of the morbidity and healthcare costs associated with type 2 diabetes. However, there is compelling evidence that comprehensive interventions can reduce the incidence and progression of these complications [23, 38, 39]. Longer-term cardiovascular risk may also be reduced with attention to glucose control [20, 40]; however, tailoring of glycaemic targets to individual circumstances is an important consideration, particularly in the older population [24, 26, 41]. These observations suggest that early, and ongoing, intervention from a physician with expertise in the management of type 2 diabetes and its complications will be important in this patient cohort.

In contrast, the evidence base for interventions following ICU discharge is more limited. Because survivors of critical illness experience profound physical symptoms for prolonged periods of time after discharge, programmes of follow-up care have been proposed to alleviate the burdens of survivorship [42, 43]. There are, however, no data to support the use of ICU follow-up clinics [44, 45]. Not only are there few randomised controlled studies, but the existing studies have employed a variety of interventions and outcome measures, compromising direct comparison [44]. The largest study to date enrolled 286 ICU survivors and randomised them to a nurse-led intensive care follow-up clinic or standard care [45]. Twelve months after ICU discharge, there was no evidence of benefit for patients randomised to the follow-up programme and the programme was, accordingly, not cost effective. A more recent multi-centre study evaluated a hospital-based rehabilitation programme of increased physical and nutritional therapies, combined with provision of illness-specific information, after ICU discharge [46]. The intervention had no effect on mobility, self-reported symptoms or health-related quality of life (HRQoL) at either 3 months, or at the 12-month follow-up. The lack of effect observed in these studies may represent a true result or a type II error. Importantly, it should be recognised that these programmes, as is the case with the majority of studies in this field of research, were conducted in heterogeneous patient cohorts and the inclusion of patients with numerous and multiple chronic diseases, many of which may be outside the sphere of expertise of healthcare professionals practising in intensive care, may have contributed to the apparent lack of benefit. Furthermore, the largest study [45] included patients with only an overnight stay in ICU and it is plausible that patients with greater illness severity and longer ICU stays are most likely to benefit from a follow-up intervention. Accordingly, in the proposed study, the health service intervention will be applied to a defined group of survivors (patients with type 2 diabetes who have had a significant ICU stay) and will utilise physicians with distinct, but complementary, expertise.

Despite the limited evidence, ICU follow-up clinics have proliferated in many countries, and generally in an ad hoc fashion, rather than in a systematic framework with rigorous evaluation of benefit [44]. However, international guidelines recommend that all ICU survivors are reviewed 2 to 3 months following hospital discharge at a follow-up clinic [47]. Given the considerable expenditure of such a health service programme, it is essential that its potential effectiveness is established and quantified, prior to implementation.

### Study objectives

The objective of this study is to establish the feasibility of conducting a definitive trial to evaluate the benefits of a shared care intensivist and diabetologist-led clinic for ICU survivors with pre-existing type 2 diabetes. Feasibility will be established by quantifying:(i)Study processes—the rate of recruitment of study participants using the proposed inclusion and exclusion criteria over 12–18 months and the rate of retention of the participants for a 6-month period(ii)Resources required—an accurate estimate of time and budget requirements(iii)Scientific effects—preliminary data relating to the potential effects of critical illness on chronic glucose metabolism, the prevalence of complications and the impact on healthcare utilisation and quality of life in intensive care survivors with type 2 diabetes. These data are necessary for confirmation of our initial calculation of sample size for the major study.

